**Site Principal Investigator**

**[name]**

Salus University, Pennsylvania College of Optometry

[name]

[name]

[contact]

Email: [[contact]](mailto:[contact])

**Overview:** **Convergence Insufficiency in Post-Concussive Symptoms study is funded via the NIH R01 EY023261.** Currently, the protocol described below is approved by CHOP IRB where NJIT and Rutgers have agreed to have CHOP be the IRB of record. The original CHOP proposal will be submitted for reference with the following modifications.

**Proposed modifications from original IRB:** NJIT is the primary institution funded via the NIH and hence it would be better for NJIT to be the lead institution for IRB. To facilitate recruitment, another clinical site (The Eye Institute of Salus University) has been added. Thus, there are the following three clinical sites: NJIT, CHOP and Salus. Drs. [name] and [name] will recruit for the NJIT clinical site. [name] will recruit for the CHOP clinical site and [name] will recruit for the Salus clinical site. FMRI parameters will only be conducted at the NJIT clinical site. A one-year follow-up assessment will only be conducted for the NJIT clinical site.

---

## ABBREVIATIONS AND DEFINITIONS OF TERMS

|           |                                                                    |
|-----------|--------------------------------------------------------------------|
| CI        | Convergence Insufficiency                                          |
| OBVAT     | Office-based vergence/accommodative therapy                        |
| TYP-CI    | Typically occurring convergence insufficiency                      |
| PPCS-CI   | Persistent post-concussion symptoms with convergence insufficiency |
| SCC       | Standard-community concussion care                                 |
| PPCS      | Persistent post-concussive symptoms                                |
| CISS      | Convergence insufficiency symptom survey                           |
| CISS-Con  | Convergence insufficiency symptom survey for Concussion            |
| VET       | Vergence Endurance Test                                            |
| VisQuaL-T | Vision Quality of Life with Time Survey                            |
| VR3       | Vergence Ramp and Steps, Saccades, and Smooth Pursuit test         |
| VBT       | Vestibular and Balance Therapy                                     |

---

---

---

---

## ABSTRACT

### Context:

Adolescent and young adult concussion is considered a substantial health problem in the United States, with recent research showing that about half of patients with persistent post-concussion symptoms have convergence insufficiency. While studies have examined both the neural mechanistic change and effectiveness of office-based vergence/accommodative therapy (OBVAT) for typically occurring convergence insufficiency (TYP-CI), there is currently no validated treatment for PPCS-CI, nor is there research comparing the pathology of TYP-CI and PPCS-CI. Further research is needed to evaluate whether the diagnostic and management procedures effective for TYP-CI should be utilized for PPCS-CI. This randomized controlled trial seeks to compare the neural mechanistic differences between TYP-CI and PPCS-CI as well as to determine the underlying neural mechanism of OBVAT and its effectiveness when combined with SCC.

### Objectives:

The primary objective of this study is to compare the effectiveness of SCC plus OBVAT compared to SCC only. The secondary objectives are to determine the underlying neural mechanism of OBVAT administered to patients with PPCS-CI as well as to compare the neural mechanistic differences between TYP-CI and PPCS-CI.

### Study Design:

Randomized controlled trial.

### Setting/Participants:

This study will include approximately 150 case subjects, ages 11 to 35 years, who present to the Children's Hospital of Philadelphia ([name]) [CHOP clinical site], Somerset Pediatric Group ([name]) and JFK Institute ([name]) [NJIT clinical site], Rothman Orthopedic ([name]) for a concussion 1-6 months post injury who are visually symptomatic and have a diagnoses of convergence insufficiency. Data from an additional 50 sex and age-matched (within 5 years) subjects recruited from the local community as healthy controls has already been collected.

### Study Interventions and Measures:

This study will compare the outcomes of adolescents and young adults with persistent post-concussive symptoms with convergence insufficiency who are randomized to standard-community concussion care (SCC) plus office-based vergence/accommodative therapy (OBVAT) versus those randomized to SCC alone to evaluate the effect of OBVAT in adolescents and young adults with PPCS-CI.

The primary endpoint of this study is the reduction in visual symptoms. This study will also assess the change in vision function measures and fMRI results of those that perform OBVAT compared to those who complete SCC. Additionally, this study will also assess the dose response of 12 OBVAT sessions as compared to 16 sessions.

---

---

**PROTOCOL SYNOPSIS**

---

|                                                                               |                                                                                                                                                                                                                                                                                                                                                                                                                                                                                                                                                                                                                                                                                                                            |
|-------------------------------------------------------------------------------|----------------------------------------------------------------------------------------------------------------------------------------------------------------------------------------------------------------------------------------------------------------------------------------------------------------------------------------------------------------------------------------------------------------------------------------------------------------------------------------------------------------------------------------------------------------------------------------------------------------------------------------------------------------------------------------------------------------------------|
| Study Title                                                            | Functional Mechanism of Neural Control in Post-Concussion Convergence Insufficiency                                                                                                                                                                                                                                                                                                                                                                                                                                                                                                                                                                                                                                 |
| Funder                                                                 | National Eye Institute of the National Institutes of Health NEI
R01EY023261                                                                                                                                                                                                                                                                                                                                                                                                                                                                                                                                                                                                                                             |
| Clinical Phase                                                         | Phase I                                                                                                                                                                                                                                                                                                                                                                                                                                                                                                                                                                                                                                                                                                                    |
| Study Rationale                                                        | There is currently no validated treatment for PPCS-CI nor is there research comparing the pathology of TYP-CI and PPCS-CI. Further research is needed to evaluate whether the diagnostic and management procedures effective for TYP-CI should be utilized for PPCS-CI.                                                                                                                                                                                                                                                                                                                                                                                                                                                    |
| Study Objective(s)                                                     | 
Primary
 
 
To compare the effectiveness of SCC plus OBVAT compared to SCC only.
 
 
Secondary
 
 
To determine the neural mechanism of OBVAT for PPCS-CI compared to SCC
 
To determine the effectiveness of 12 one-hour sessions compared to 16 one-hour sessions of OBVAT.
 
To compare the differences between PPCS-CI and TYP-CI.
 
                                                                                                                                                                                                                                                   |
| Test Article(s)
(If Applicable)                              | Office-based vergence/accommodative therapy plus standard-community concussion care vs. standard-community concussion care alone.                                                                                                                                                                                                                                                                                                                                                                                                                                                                                                                                                                                          |
| Study Design                                                           | Randomized controlled trial. Phase I                                                                                                                                                                                                                                                                                                                                                                                                                                                                                                                                                                                                                                                                                       |
| Subject Population
key criteria for Inclusion and Exclusion: | 
Inclusion Criteria (case subjects)
 
 
1. Males or females ages 11 – 35 years of age
 
2. Best-corrected visual acuity of 20/25 in both eyes at distance and near.
 
3. Willingness to wear glasses or contacts to correct refractive error, if needed.
 
4. Stereopsis of 500 sec arc using Randot Stereo Test.
 
5. Symptomatic PPCS-CI
 
6. Parental/guardian permission (informed consent) and if appropriate, child assent.
 
7. Diagnosis of convergence insufficiency defined as a receded near point of convergence of more than 6 cm, insufficient positive fusional vergence defined as less than 15 prism
 
 |

---

---

diopters (or positive fusional vergence less than twice the near phoria).

**Exclusion Criteria (case subjects)**

8. Previous office- or home-based vision therapy, orthoptics, home-based near-target push-ups, or pencil push-ups.
9. Amblyopia or constant strabismus or strabismus surgery.
10. High refractive error: Myopia  $\geq 6.0\text{D}$  sphere; Hyperopia  $\geq 5.0\text{D}$  sphere; Astigmatism  $\geq 4.0\text{D}$ ; Anisometropia  $>1.5\text{D}$  difference between eyes; prior refractive surgery.
11. Manifest or latent nystagmus evident clinically.
12. Systemic diseases that affect accommodation, vergence or ocular motility (i.e. multiple sclerosis, Graves' thyroid disease, myasthenia gravis, diabetes, chemotherapy, or Parkinson's disease).
13. Vertical heterophoria greater than  $1\Delta$ .
14. Parents/guardians or subjects who, in the opinion of the Investigator, may be non-compliant with study schedules or procedures.
15. Exclusion Criteria for NJIT site only:
  - A. Non-removable metal in the body.
  - B. Subjects who are pregnant, planning on becoming pregnant during the study duration, or breastfeeding.
  - C. Subjects who are metal workers.

---

|                           |                                                                                                                                                                                                                                |
|---------------------------|--------------------------------------------------------------------------------------------------------------------------------------------------------------------------------------------------------------------------------|
| Number Of Subjects | Approximately 200 subjects will be tested for eligibility in the study to ensure approximately 150 evaluable subjects complete the longitudinal study.                                                                         |
| Study Duration     | Each subject's participation will last until the completion of their OBVAT sessions. For arm 1 cases, their participation will last 11 weeks +/- 3 weeks. For arm 2 cases, their participation will last 17 weeks +/- 3 weeks. |

---

---

---

|                                                                                       |                                                                                                                                                                                                                                                                                                                                                                                                                                                                                                                                                                                                                                                                                                                                                                                                                                                                                                                                                                                                                                                                                                                                                                                                                                                                                                                                                                                                                                                                                                                                                                                                                                                                                                                                                                                                                                                                                                                                                                                                                                                                                                                                                                                                                                    |
|---------------------------------------------------------------------------------------|------------------------------------------------------------------------------------------------------------------------------------------------------------------------------------------------------------------------------------------------------------------------------------------------------------------------------------------------------------------------------------------------------------------------------------------------------------------------------------------------------------------------------------------------------------------------------------------------------------------------------------------------------------------------------------------------------------------------------------------------------------------------------------------------------------------------------------------------------------------------------------------------------------------------------------------------------------------------------------------------------------------------------------------------------------------------------------------------------------------------------------------------------------------------------------------------------------------------------------------------------------------------------------------------------------------------------------------------------------------------------------------------------------------------------------------------------------------------------------------------------------------------------------------------------------------------------------------------------------------------------------------------------------------------------------------------------------------------------------------------------------------------------------------------------------------------------------------------------------------------------------------------------------------------------------------------------------------------------------------------------------------------------------------------------------------------------------------------------------------------------------------------------------------------------------------------------------------------------------|
| Study Phases
Screening
Study Treatment
Follow-Up | 
Screening and Initial Assessment: All patients who present to the Children’s Hospital of Philadelphia, Somerset Pediatric Group, JFK Institute or Rothman Orthopedic with a concussion date of injury 1-6 months ago will be screened for enrollment as case subjects using the protocol inclusion and exclusion criteria. Clinicians specializing in concussion management will identify potential subjects under their care in clinics after a standard clinical evaluation that consists of a detailed history and examination. A member of the study team will introduce the study to subjects deemed eligible to participate, obtain verbal consent to screening, and screen them against study inclusion and exclusion criteria. Eligible subjects will have time to ask questions and consider participation prior to consenting. Parental/guardian permission (informed consent) and, if applicable, child assent, will be obtained prior to any study related procedures being performed. After consenting to participate, subjects will complete an initial optometric exam, vision assessments, fMRI (NJIT site only), and a patient-reported symptom questionnaire. Data from control subjects recruited from local colleges and universities who did not have a recent concussion have already been collected.
 
Intervention: Case subjects will be randomly assigned into one of two arms. Arm 1 will begin OBVAT immediately, while arm 2 will start with 6 weeks of SCC followed by the OBVAT intervention. A member of the study team will connect subjects with the study vision therapist who will perform their OBVAT sessions. Arm 1 subjects will complete 12 1-hour bi-weekly OBVAT sessions with the vision therapist in addition to SCC while arm 2 subjects complete SCC alone. After 6 weeks, subjects will complete outcome visit 1. After outcome visit 1, arm 1 cases will complete 4 more OBVAT sessions and then complete outcome visit 2. After the initial 6 weeks, arm 2 cases will complete 16 1-hour bi-weekly OBVAT sessions and then complete outcome visit 2. All case subjects will complete at-home reinforcement activities during their OBVAT intervention.
 |
| Efficacy Evaluations                                                           | 
Change in symptoms over the course of the intervention.
 
Rate of symptom remediation in OBVAT+SCC group compared to SCC alone.
                                                                                                                                                                                                                                                                                                                                                                                                                                                                                                                                                                                                                                                                                                                                                                                                                                                                                                                                                                                                                                                                                                                                                                                                                                                                                                                                                                                                                                                                                                                                                                                                                                                                                                                                                                                                                                                                                                                                                                                                                                                                                        |

---

|                                        |                                                                                                                                                                                                                                                                                                                                                                                                                                                                                                                                                                                          |
|----------------------------------------|------------------------------------------------------------------------------------------------------------------------------------------------------------------------------------------------------------------------------------------------------------------------------------------------------------------------------------------------------------------------------------------------------------------------------------------------------------------------------------------------------------------------------------------------------------------------------------------|
|                                        | Change in vision function and fMRI measures (NJIT site only).                                                                                                                                                                                                                                                                                                                                                                                                                                                                                                                            |
| Safety Evaluations              | A trained and annually certified vision therapist will monitor all subjects during their OBVAT sessions to ensure that the sessions are being performed safely. Patient-reported symptoms will be monitored during each OBVAT session. [name] has over 45 years experience with OBVAT and will be training and certifying vision therapists. He will be available for any questions. In prior large scale randomized clinical trials studying OBVAT on neurologically normal children and young adults under [name] leadership, no adverse effects were reported. |
| Statistical And Analytic Plan   | A Wilcoxon signed test will determine whether significant changes occur between the true mean measurement after OBVAT+SCC or SCC only. A paired t -test will also be used due to its robustness property as a justifiable comparison. The direct treatment effects due to interactions between groups and time periods (before and after therapy) will be analyzed with post-hoc tests such as Tukey's method. Adjustments for multiple comparisons will be done to ensure an error rate $\alpha$ -level of 0.05.                                                                 |
| DATA AND SAFETY MONITORING PLAN | The PI will assure that the privacy of subjects, including identity and medical information, will be maintained at all times. In addition, the PI and [name] will oversee the study team and will actively monitor the study to ensure that it is carried out safely and that a subjects' symptoms do not increase sharply or over an extended period of time as a result of participation. A physician in the concussion clinic will examine any case subject that appears to show a regular increase in symptoms over the course of the study.                 |

---

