## **6 STATISTICAL CONSIDERATIONS**

### **6.1 Primary Endpoint**

The primary endpoint will be the change in composite clinical parameters of near point of convergence and positive fusional vergence between the initial assessment and the outcome visits.

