#### **6.3.2 Efficacy Analysis**

The primary analysis will be based on an intention to treat approach and will include all subjects randomized at their initial assessment.

The primary efficacy endpoint will be the change in composite clinical parameters of near point of convergence and positive fusional vergence between the initial assessment and the outcome visits. A repeated measures ANOVA will be used to assess the clinical parameters as well as the chi-squared test using predetermined published optometric benchmarks for improvement.

Secondary endpoints will include the rate of symptom remediation in OBVAT+SCC group compared to SCC alone, change in vision function, and fMRI measures between the start and end of the treatment phase.

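### The synopsis calls the group-by-time interaction the treatment effect but assigns it to Tukey-type post-hoc comparisons, and section 6.3.2 does not tie the treatment test to that interaction or to Outcome Visit 1

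*Protocol*

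**What the plan says.** In the Protocol Synopsis, the row on the statistical and analytic plan names a Wilcoxon signed test and adds: "A paired t -test will also be used due to its robustness property as a justifiable comparison". It then identifies the direct treatment effect with the interaction of group and time period, and assigns it to follow-up comparisons: "The direct treatment effects due to interactions between groups and time periods (before and after therapy) will be analyzed with post-hoc tests such as Tukey's". The row ends: "Adjustments for multiple comparisons will be done to ensure an error rate $\alpha$ -level of 0.05".

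Section 6.3.2 reads: "A repeated measures ANOVA will be used to assess the clinical parameters as well as the chi-squared test using predetermined published optometric benchmarks for improvement". It does not say which ANOVA term is the test of treatment. Section 6.1 defines the primary endpoint as "change in composite clinical parameters of near point of convergence and positive fusional vergence between the initial assessment and the outcome visits", with the visits in the plural. Under section 4.2, arm 2 has had only SCC at Outcome Visit 1, but has completed 16 OBVAT sessions by Outcome Visit 2. The synopsis row and section 6.3.2 do not refer to each other.

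**The concern.** The interaction asks whether change from before to after differs between the arms. Its null hypothesis is equal change. Tukey's method applied to the four group-by-time means tests six pairwise differences, and none of them is that difference of differences. The before-after pairs are non-null whenever subjects improve, with or without a treatment effect.

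No other test in the synopsis row fills the gap. The signed-rank and paired t-tests are for paired data, and the randomised arms are different subjects. The ANOVA in section 6.3.2 could fill it, but its deciding term and visit are not stated. At Outcome Visit 2 both arms have had OBVAT, so a contrast there no longer compares OBVAT+SCC with SCC alone.

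Two things are at stake. A change in one arm without a significant change in the other could be reported as a treatment effect. A real effect could also be missed if the after-versus-after pair is the one that is read.

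**Working it through.** **No plan figure to reproduce.** The protocol states no power for a between-arm contrast. Section 6.4 sizes the trial with paired t-tests and gives standard deviations but no effect size. Its correlations are described for placebo therapy and OBVAT, not for before and after.

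**Inputs from the protocol.** 150 evaluable subjects (section 6.4) at 1:1 (section 9.1.1) give n = 75 per arm. Section 6.4 also names 50 per arm. Alpha is 0.05, taken as two-sided.

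**Assumptions.** Normal data, SD 1, pre/post correlation r = 0.3, 0.5 or 0.7, common recovery 0.2, 0.4 or 0.6 SD, and treatment effect 0 or 0.5 SD. Tukey is applied to four cells with pooled cell variance. Its critical value on the t scale (studentized range divided by √2) is 2.584 at n = 75 and 2.591 at n = 50.

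**Step 1: recovery, no treatment effect.** A before-after pair is significant with probability p ≈ Φ((recovery × √(n/2) − critical value) / √(1 − r)). The arms are independent, so arm 1 alone is significant with probability p(1 − p), which cannot exceed 25%.

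For n = 75, recovery 0.4 and r = 0.5: 0.4 × √37.5 = 2.449; (2.449 − 2.584)/0.707 = −0.190; p = 0.425; p(1 − p) = 24%.

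| Recovery, n = 75 | r = 0.3 | r = 0.5 | r = 0.7 |
|---|---|---|---|
| 0.2 SD | 4.9% | 2.7% | 0.6% |
| 0.4 SD | 24.6% | 24.4% | 24.1% |
| 0.6 SD | 8.7% | 5.8% | 2.3% |

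The worst recovery size depends on n. At n = 50 the same formula gives 12% to 18% at 0.4 SD and 18% to 21% at 0.6 SD.

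By simulation at n = 75 and 0.4 SD, at least one of the six pairs is significant in 81% to 86% of trials, while the interaction test rejects in about 5%. The after-versus-after pair is untouched by recovery: its error is 2Φ(−2.584) ≈ 1%.

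**Step 2: power at a 0.5 SD effect, n = 75.**
- After-versus-after Tukey pair: Φ(0.5 × √37.5 − 2.584) = Φ(0.478) = 68%, whatever r is.
- Interaction (difference in change): Φ(0.5 × √(75/(4(1 − r))) − 1.98). This is Φ(0.608) = 73%, Φ(1.082) = 86% and Φ(1.973) = 98% at r = 0.3, 0.5 and 0.7.
- Equal power requires 0.5 × √(75/(4(1 − r))) = 0.478 + 1.98 = 2.458, so r ≈ 0.22. Below that the Tukey pair is the stronger; at r = 0 it has 68% against 57%.

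At n = 50 the Tukey pair has 46%, against 55%, 70% and 89% for the interaction, and the crossing is at r ≈ 0.12.

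**Step 3: baseline-adjusted difference.** Its variance is proportional to 1 − r², against 2(1 − r) for the change-score contrast. The ratio is (1 + r)/2: 0.65, 0.75 and 0.85 at the three correlations. Power at n = 75 is Φ(0.5 × √(37.5/(1 − r²)) − 1.98) = 89%, 94% and 99%, and 86% at r = 0. It exceeds the Tukey pair at each of these correlations.

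**The case against.** The strongest reply is that post-hoc tests, by name, follow an omnibus model, and section 6.3.2 supplies one: "A repeated measures ANOVA will be used to assess the clinical parameters as well as the chi-squared test". A repeated measures ANOVA with two arms contains the group-by-time test. Read together, the two places can describe ANOVA, then interaction, then Tukey as follow-up, which is conventional. With that sequence the false arm-1-only pattern at 0.4 SD recovery falls to about 2% to 3%. Tukey is also only an example; the protocol fixes no cells, pairs or error term, and Tukey applied to two arms' change scores is exactly the t-test on change.

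Much of this stands. It rules out some stronger readings that a reader might infer:
- *That the trial has a false-positive rate of 81% to 86%.* The before-after rejections behind that figure are correct rejections of their own null hypotheses, and nowhere does the protocol say that any significant pair establishes efficacy.
- *That Tukey always loses power.* This depends on a pre/post correlation that the protocol does not give, and on which pair is read.
- *That the trial has no between-arm analysis.* The ANOVA and the chi-squared test can each supply one.

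What the reply does not remove is the sentence itself. It assigns the stated treatment effect to the follow-up procedure. Section 6.3.2 does not correct it, because it ties the treatment test neither to the interaction nor to Outcome Visit 1. Leaving model detail to a statistical analysis plan is normal, but here the protocol affirmatively names a procedure that does not match its own stated effect.

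**Conclusion.** The point holds in a limited form. The synopsis names the right effect and attaches a procedure that does not test it, and section 6.3.2 is compatible with the right test without stating it. The harm is conditional on the Tukey pairs being read as the treatment test. In that case a misleading arm-1-only pattern arises in at most about 25% of trials, and about 1% to 9% at recoveries of 0.2 or 0.6 SD with 75 per arm. The after-versus-after pair gives up about 4 to 29 percentage points of power at correlations of 0.3 to 0.7, and gains at correlations below about 0.2. Recovery size, effect size and correlation are all assumptions. Some recovery under standard care is plausible: section 1.3 cites persistent symptoms falling from 46% at two weeks to 33% at four weeks. The change is worth making because it is cheap and also settles which visit carries the randomised comparison.

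**What to change.** Align the synopsis row and section 6.3.2 on these points:

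1. The treatment test for each endpoint is one prespecified between-arm contrast from initial assessment to Outcome Visit 1, with a 95% confidence interval and a two-sided 0.05 test. The baseline-adjusted difference is preferable. It is not the same estimator as the change-score interaction, and it is generally more precise, so the text should say which one is meant.
2. Tukey comparisons of group-by-time means are follow-up only and are not evidence of a treatment effect.
3. A separate prespecified comparison of Outcome Visit 1 with Outcome Visit 2 within arm 1 is kept for the objective on 12 versus 16 sessions. Without it, point 2 would remove that analysis from inference.

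The cost is one sentence in the synopsis and one or two in section 6.3.2. No new data, visits or subjects are needed. What is given up is the use of within-arm before-after p-values as evidence for OBVAT over SCC.
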